**Figure 1 F1:**
[figure not shown]
Test flow chart.

Potential participants will be invited to an initial assessment (first visit) consisting of an inclusion and exclusion criteria screening. If eligible, participants will be asked for informed consent and will undergo assessment of Psoriasis area severity index (PASI), dermatology life quality index (DQOLS), and score of Pruritus Degree by PGA, lesion photos and vital signs, full blood count, kidney and liver function blood tests, electrocardiogram, stool examination and urine (routine chemical examinations).

A total of 72 patients with recurrent PV will be randomized (in a 1:1 ratio) to receive oral Chinese herbal medicine JWLXXF or oral acitretin for 8 weeks. During the observation phase, psoriasis symptom measures will be self-reported by participants and recorded in a daily or weekly diary. Face-to-face assessments with blinded assessors will be scheduled at weeks 2, 4, 6, and 8 (Fifth visit), with further data collected, including assessment of PASI, DQOLS, and score of Pruritus degree by PGA, lesion photos, drug adherence, vital signs, adverse events and cause analysis of shedding (Table 1). The conversation will be made to 72 patients, at the time of medical treatment, to check adherence to the dosage guidelines and to monitor adverse events. Routine chemical examinations, laboratory assessments of efficacy and safety evaluation will also be scheduled at the end of the 8-week period.

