#### Inclusion criteria

3.1.1

Patients will be included if they satisfy the following criteria:

(1)comply with the diagnostic criteria for psoriasis vulgaris as indicated in dermatovenerology 8th Edition;(2)comply with the diagnostic criteria for blood-heat syndrome as indicated in the Guidelines for the Clinical Research of Chinese Medicine New Drugs and New Dermatology of Traditional Chinese Medicine;(3)must be aged between 18 and 70 years;(4)An informed consent is provided; and(5)recurrent psoriasis patients must belong to the types of recurrence IV, V and VI^[12,13]^: Type IV (frequently limited type): The rash is extensive or limited at the first onset, and rashes occur every year afterward, but the amount of rash is small and is limited to certain parts of the body; Type V (frequently sparsely sparse): Psoriasis often recurs, with a wide range of rashes at the onset, but with a sparse density; Type VI (frequently issued): Psoriasis occurs every year, and the rash is widely distributed and numerous.

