#### Primary outcomes

3.5.1

(1)PASI: assess the severity of the disease.(2)Laboratory assessments: the number and distribution of Th1, Th2, Th17, Treg, Th22, and Th9 cells will be determined by ELISA. The expression of the transcription factors T-bet, GATA3, ROR gamma t, Foxp3 gene will be investigated by PCR and WB. The screening of cytokines, such as IFN-gamma, IL-4, IL-17A, IL-17F, IL-22, TGF-beta, IL-10 and IL-9 will be performed by Bio-Plex suspension chip.(3)Recurrence rate = recurrence cases/follow-up cases ∗100%

Note:

No recurrence criteria: the same as the end of treatment and lesion limitation. Recurrence criteria: new skin lesions appearing in the patients who were clinically cured or have the original skin lesions expanding, the color turning red, the scale increasing and the PASI score increasing for ≥ 1.

(1) Mitigation period: this remission period - the last remission period.

Note:

The last remission period: the time from the last clinical cure to the recurrence. This remission: the time interval from the end of JWLXXF treatment to the next recurrence.

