### Sample size calculation

3.8

Due to the unknown potential primary outcome at this stage, the sample size was calculated by reference to a standardized effect size. An effect size of 0.9 SD was chosen with consideration of the drug cost and patients’ motivation to adhere to the treatment. To detect a difference of 0.9 SD with 90% power using a 5% significance level, a sample size of 30 per arm would be required. Considering 20% dropout rate, the total sample size should be adjusted to 36 for each group.

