### Statistical analysis

3.10

SPSS Statistics 17.0 (IBM SPSS Inc., Armonk, NY) will be used for the statistical analysis of data, which will be carried out by independent statisticians. The Chi-square test will be used to evaluate the basic baseline characteristics and primary outcomes of the 2 groups. The Spearman rank correlation analysis of the correlation between PASI and biochemical indexes, will be used. The secondary outcomes will be evaluated by means, standard deviations and medians. The one way ANOVA test will be used to compare the mean of multiple samples, the LSD test for the homogeneous variance, and the Tamhane T2 test for the uneven variance. *P* < .05 will be considered as statistically significant.

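### Section 3.10 gives PASI, a severity score with no declared cut, a chi-square test; under a normal model that caps power near 79% at 30 per arm, against about 93% for a continuous comparison.

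*Protocol article*

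**What the plan says.** All references are to the protocol article.

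- **Test (3.10).** "The Chi-square test will be used to evaluate the basic baseline characteristics and primary outcomes of the 2 groups". No primary outcome is exempted.
- **Outcome (3.5.1).** The first primary outcome is given as "PASI: assess the severity of the disease", with no cut and no responder form. Recurrence rate, which is categorical, is in the same list.
- **Other methods (3.10).** PASI is treated as graded when it is related to the laboratory data: "The Spearman rank correlation analysis of the correlation between PASI and biochemical indexes, will be used". For means, "The one way ANOVA test will be used to compare the mean of multiple samples", with LSD or Tamhane T2 as follow-up tests. That sentence names no outcome.
- **Sample size (3.8).** "Due to the unknown potential primary outcome at this stage, the sample size was calculated by reference to a standardized effect size". The target is "To detect a difference of 0.9 SD with 90% power using a 5% significance level", which leads to 30 per arm, raised to 36 for dropout.
- **PASI75.** A 75% improvement is the entry rule for follow-up (section 2) and the short-term efficacy standard in the discussion (4.2). It is not given as the form of the primary outcome.
- **Data available.** PASI is taken at the initial assessment, and then "Face-to-face assessments with blinded assessors will be scheduled at weeks 2, 4, 6, and 8" (section 2).

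**The concern.** The text gives a graded score a test for categories and does not say where the categories lie. Whichever cut is chosen later, patients on the same side of it count as equal, so information that the trial already collects is discarded. The only effect size in the plan is on a continuous scale, so the power reasoning and the stated test do not match.

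The stake is a missed difference. Under the normal model worked below, a true 0.9 SD difference would be missed in about one trial in five at the most favourable cut (1 − 0.791 = 0.209), against about one in fourteen with a t-test (1 − 0.929 = 0.071). Leaving the cut open also allows it to be chosen after the data are seen.

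**Working it through.** **Inputs from 3.8:** difference 0.9 SD, 5% significance level (two-sided assumed, since the sidedness is not stated), 30 evaluable per arm, 36 randomised per arm. **Assumptions not in the document:** the 0.9 SD applies to PASI, and the two arms are normal with equal SD. The article gives no PASI75 rate or PASI SD, so control response rates are shown as a range.

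**1. The plan's own figure.** The normal formula, n = 2(1.960 + 1.282)²/0.9², gives 26 per arm. The noncentral t needs 27 (power 0.901). The stated 30 is somewhat generous: t-test power at 30 is 0.929, and at 36 it is 0.965 (0.9645).

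**2. One cut, then chi-square.** If the control response rate is p1, a 0.9 SD shift gives p2 = Φ(Φ⁻¹(p1) + 0.9). Power at 30 per arm:

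| p1 | p2 | Pooled normal approximation | Exact, uncorrected chi-square |
|---|---|---|---|
| 0.05 | 0.228 | 0.514 | 0.558 |
| 0.10 | 0.351 | 0.651 | 0.666 |
| 0.20 | 0.523 | 0.754 | 0.754 |
| 0.30 | 0.646 | 0.781 | 0.789 |
| 0.40 | 0.741 | 0.775 | 0.779 |
| 0.50 | 0.816 | 0.744 | 0.746 |
| 0.70 | 0.923 | 0.601 | 0.623 |

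The maximum over all cuts is at p1 = 0.326, p2 = 0.674: 0.782 by approximation and 0.791 exact. With the Yates correction or Fisher's test it is 0.705. The loss against the t-test is 0.929 − 0.791 = 0.138, about 14 points. If all 36 per arm are evaluable, the best cut gives 0.844 (exact) to 0.854 (approximation), against 0.965.

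**3. More categories.** Pearson chi-square in simulation at 30 per arm: pooled tertiles 0.788, pooled quartiles 0.764. Extra categories do not recover the loss.

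**4. Dependence on normality.** Same 0.9 SD shift, 30 per arm, best cut, exact uncorrected chi-square:

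| Distribution | Best-cut power |
|---|---|
| Normal | 0.791 |
| Logistic | 0.874 |
| t with 5 df | 0.916 |
| Laplace | 0.971 |

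The simulated t-test has 0.929 under the logistic and 0.923 under the Laplace distribution. With Laplace tails the ideal cut therefore beats the t-test. These figures are for the best cut, and PASI75 need not fall there.

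**5. Scale for the continuous analysis.** Section 3.1.1 admits Type IV patients, of whom it says "but the amount of rash is small and is limited to certain parts of the body", together with patients whose rash is widespread. Baseline PASI may therefore be spread widely and the effect may be proportional. Model: 0.9 SD shift on log(week 8/baseline), assumed baseline log-SD 0.6, log-ratio SD 0.3, 0.5 or 1.0, 30 per arm. Simulated power is 0.92 to 0.93 for log-scale ANCOVA and 0.91 to 0.92 for a rank test on percentage change. For raw-scale ANCOVA it is about 0.80, 0.78 and 0.68. The scale has to be named in advance.

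**The case against.** **The authors may have meant PASI75 or recurrence.** Chi-square is valid for both, and a responder endpoint tied to a new-drug standard is a legitimate choice. This stands in part, and it is why chi-square should stay for recurrence and for PASI75. But 3.5.1 does not define PASI as PASI75, and PASI75 is itself one cut, with the same ceiling under the normal model.

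**The ANOVA sentence may cover PASI.** It names no outcome, and its follow-up tests serve three or more groups. If it was meant for PASI, 3.10 gives the same comparison two tests and still needs the clarification.

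**The sentence is shorthand in a condensed article.** Read literally, it also puts cytokines and remission time under chi-square, so this is plausible. Still, the article does state a test for the primary outcomes, and the stated test does not suit PASI as listed.

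**A stronger reading is tempting:** that no cut whatever could exceed 79%, and that the trial therefore breaks its 90% promise for PASI. The documents do not support either half. Section 3.8 states no distribution, and step 4 shows the ceiling rising with heavier tails. Section 3.8 also says the outcome was unknown and uses a generic effect size, so it makes no promise about PASI in particular.

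**Conclusion.** The point holds in a conditional form. Following 3.10 as written means categorising PASI at an undeclared cut, and that discards information under the usual reading of a 0.9 SD effect. The size is about 14 power points at the best cut (79% against 93% at 30 per arm), and more at cuts away from the middle, down to 56% at a 5% control response rate. Three assumptions carry these figures: the 0.9 SD applies to PASI, the shift is normal with equal SDs, and the chi-square test is uncorrected. With logistic tails the loss at the best cut shrinks to about 6 points (93% against 87%), and with Laplace tails it disappears. This should be corrected because the remedy is cheap. It does not show that the trial is underpowered against its own stated target.

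**What to change.** Rewrite the first analysis sentences of 3.10 along these lines:

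1. Use the chi-square test for categorical outcomes, such as recurrence yes/no.
2. Compare week-8 PASI between arms by ANCOVA on log(PASI + c), with the constant c fixed before arms are compared and baseline log PASI, computed with the same constant, as covariate. Report the adjusted ratio with its 95% confidence interval.
3. Pre-specify a rank test on percentage change in PASI as a sensitivity analysis.
4. Report PASI75 by arm with chi-square as supportive.
5. Leave the PASI75 rule for entry into follow-up unchanged.

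The cost is a few lines of text. No visit, measurement or patient is added, because baseline and week-8 PASI are already scheduled. Section 4.4 reports 60 patients recruited so far, so the change can still be made before the arms are compared. The downside is that an adjusted PASI ratio is harder to read than a response rate, which is why PASI75 stays in the report. Keeping a single cut as the main analysis would instead need at least 42 evaluable per arm for 90% power under the normal model (normal approximation), and 57 at a 10% control response rate.

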**Methods and analysis::**

This is a pilot randomized controlled trial with the objective of investigating the effect of Jia Wei Liang Xue Xiao Feng San granules on relapse rate of recurrent PV and the correlation between Psoriasis area severity index (PASI) and key psoriasis-related cytokine changes and the number of cells. A total of 102 participants were recruited for this study, including 72 patients with recurrent PV, 15 healthy volunteers and 15 patients with psoriasis vulgaris who have recovered for more than 1 year. A total of 72 patients, with recurrent PV, will be randomized (1:1) to receive the oral Chinese herbal medicine Jia Wei Liang Xue Xiao Feng San or the oral Acitretin Capsule treatments for a period of 8 weeks. After this period, participants whose PASI scores improvement reached more than 75%, will undergo a 52-week follow-up phase.

The primary outcome measures are as follows:

The secondary study outcomes will include:

This trial may provide a novel regimen for recurrent PV patients if the granules decrease recurrence rate without further adverse effects.

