There are very few studies that investigated psoriasis mechanism of recurrence at home and elsewhere. The Carrascosa et al^[5]^ study found that the decrease in the number of CD4 cells was statistically significant with a persistent psoriasis remission. Casteljns et al^[6]^ confirmed that keratin 16 is significantly expressed in the asymptomatic skin, adjacent to a recurrent lesion, that Ki-67 expression increased at the edge of skin lesions and that keratin 14 is expressed in recurrent lesions at the initial recurrence stage of psoriasis. Flisiak et al^[7]^ confirmed that plasma IL- 18 concentration was associated with the severity of psoriasis and that the combined determination of plasma IL- 18 and TGF -β1 can be used as a possible sign of psoriasis activity. Friedrich et al^[8]^ also confirmed that the treatment with the immunoregulating IL-10 can reduce the recurrence rate and prolong the interval of psoriasis recurrence. We believe that the immune mechanism of psoriasis recurrence mainly focuses on the innate immune and acquired immune systems. A large number of basic studies have shown that psoriasis is an organ-specific inflammatory disease, where T cells dominate its pathogenesis and persist its inflammatory status.^[9]^

According to the traditional Chinese medicine theory and clinical observation, the Chinese medicine compound Jia Wei Liang Xue Xiao Feng San (JWXXF) was developed by a renowned Chinese herbal medicine clinician ([name]), and that the experimental results confirmed that^[10,11]^ JWXXF can have a positive effect in psoriasis treatment by inhibiting KC keratinization, preventing inflammation, inhibiting PCNA expression and regulating TNF-1. Therefore, a rigorously designed, randomized and controlled trial to investigate the possibility and degree of JWLXXF granules to reduce recurrence rate and to provide immunological basis for JWLXXF granules application in psoriasis recurrence treatment is required.

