**Table 1 T1:**
[figure not shown]
Evaluation measures and time points.

The 72 patients with recurrent PV, whose PASI scores improvement are more than 75%, will undergo a 52-week follow-up phase (week 9 to week 60), with further data collection, including assessment of PASI, routine chemical examinations, recurrence rate, remission period (This remission period - the last remission period) (Table 1).

For the 52-week follow-up phase, participants will continue to record symptoms in their daily or weekly diaries. At week 60, participants will attend an end of follow-up assessment (9th visit) which will mark the end of the trial.

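### The one association analysis stated for the immune markers, an unadjusted Spearman correlation with PASI, commits neither to marker changes nor to arm adjustment, and nothing relates markers to recurrence.

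*Protocol article*

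**What the plan says.** The abstract gives two objectives: the effect on relapse rate, and "the correlation between Psoriasis area severity index (PASI) and key psoriasis-related cytokine changes and the number of cells". The Introduction adds a second purpose for the laboratory work, saying that a trial "to provide immunological basis for JWLXXF granules application in psoriasis recurrence treatment is required". Section 4.3 likewise presents the cell, protein and gene measurements as bearing on how the compound prevents recurrence.

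The markers are not a side measure. Section 3.5.1 lists them as a primary outcome, beginning "Laboratory assessments: the number and distribution of Th1, Th2, Th17, Treg, Th22, and Th9 cells will be determined by ELISA", followed by four transcription factors and eight named cytokines. Recurrence rate is in the same list.

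Section 3.10 has three sentences that can touch the markers:
- Association: "The Spearman rank correlation analysis of the correlation between PASI and biochemical indexes, will be used".
- Group comparison: "The Chi-square test will be used to evaluate the basic baseline characteristics and primary outcomes of the 2 groups".
- Several means, variables not named: "The one way ANOVA test will be used to compare the mean of multiple samples".

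The Spearman sentence fixes no visit, no change score and no handling of arm. No sentence links a marker to recurrence or to length of remission.

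**The concern.** A correlation computed over two treatment groups mixes two things: whether patients with a larger PASI response also have a larger marker response, and whether the two groups differ on average in both. Only the first supports a claim that a marker tracks disease activity. The second appears whenever the treatments differ in their effect on both variables, even if the two are unrelated among patients on the same treatment. Combining visits creates the same problem through time, because PASI is expected to fall over the 8 weeks and any marker that also drifts will then appear to be linked with it.

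Two things are at stake. A marker could be reported as a correlate of psoriasis activity only because both variables moved with treatment. And whether immune state at the end of treatment relates to later relapse, one of the two purposes given for the laboratory work, has no stated analysis.

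**Working it through.** **Plan figures.** The article gives no figure for the correlation analysis. Section 3.8 supplies the group size (30 per arm, 36 after the dropout allowance) and an effect size of 0.9 SD. As a check, n = 2(1.960 + 1.282)² / 0.9² = 25.9, so 26 per arm, or 27 by the t-test version. The stated 30 is somewhat generous, and nothing below depends on that.

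**1. Arms combined, no link within arm.** Let PASI and the marker be independent within each arm, each with SD 1, and both shifted by d SD between two equal arms. These may be week-8 values or changes. Over the combined arms the covariance is d²/4 and each variance is 1 + d²/4, so

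r = (d²/4) / (1 + d²/4).

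- d = 0.5: 0.0625 / 1.0625 = 0.06
- d = 0.9: 0.2025 / 1.2025 = 0.17
- d = 1.5: 0.5625 / 1.5625 = 0.36

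Simulation of the Spearman test (3,000 trials per row, two-sided 5%) agrees closely:

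| Shared shift | Mean rho, 30 per arm | P < .05, 30 per arm | P < .05, 36 per arm | After removing arm means |
|---|---|---|---|---|
| 0 | 0.00 | 5% | 5% | 5% |
| 0.5 SD | 0.06 | 8% | 8% | 5% |
| 0.9 SD | 0.17 | 25% | 30% | 5% |
| 1.5 SD | 0.38 | 86% | 93% | 4–5% |

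A separate repeat at 0.9 SD gave 24%.

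The shift sizes are assumptions. The 0.9 SD is the plan's own effect size, applied here to both variables. Because both arms are active, the true shift between arms may be small, so the 0.5 and 0.9 SD rows are the more relevant ones.

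**2. Baseline and week 8 pooled (assumption).** Take 60 patients, PASI and marker independent, within-patient correlation over time 0.6, no arm difference, and 2,000 trials per row. With shifts a and b the expected correlation is (ab/4) / √[(1 + a²/4)(1 + b²/4)]. For a = 2 and b = 1 this is 0.5 / √(2 × 1.25) = 0.32.

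| PASI shift, marker shift (SD) | Mean rho | P < .05 |
|---|---|---|
| 1.5, 0.5 | 0.14 | 34% |
| 2, 0.5 | 0.18 | 49% |
| 1.5, 1 | 0.28 | 87% |
| 2, 1 | 0.33 | 97% |

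Repeats moved the lowest figure to 36–38%. Correlating change with change in the same data gave P < .05 in about 5%. This second simulation has no arm difference, so it supports the use of change scores; the case for arm adjustment rests on step 1.

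**3. Aims against analyses.**
- Correlation of PASI with marker changes (abstract): addressed by Spearman, but without committing to changes.
- Immunological basis for treating and preventing recurrence (Introduction, section 4.3): no stated analysis.

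**The case against.** The strongest reply is that visit, arm and change-score details are often left to an analysis plan, and none is shown. The abstract speaks of changes, so the natural reading of section 3.10 may already be change against change, which removes the artefact from pooling visits. This stands as far as it goes: pooling of visits cannot be presented as what the trial will do. But section 3.10 does state an analysis, and that statement does not match the objective's wording. Even a correlation of changes remains open to the arm effect in step 1.

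Three stronger readings are tempting, and the article does not support them:
- A reader might infer that Spearman is the only marker analysis. It is the only association analysis. The markers are primary outcomes, so the chi-square sentence nominally covers them, and the ANOVA sentence may do so.
- A reader might infer that recurrence is the purpose of the markers and that Spearman misses it. Recurrence is one of two purposes, and the correlation does address the one in the abstract.
- A reader might infer that the 30 healthy or recovered participants enter the correlation, or that no immune samples are taken in follow-up. The first is stated nowhere. On the second, the follow-up text reads "with further data collection, including assessment of PASI, routine chemical examinations, recurrence rate, remission period", an open list, and the schedule in Table 1 is not shown.

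It is also fair to object that modelling level and change of every named marker against relapse (6 + 4 + 8 = 18 markers, so 36 models) would be far too much for a pilot that follows responders only. That stands, and it limits what should be asked for.

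**Conclusion.** The point holds in a limited form. The only stated association analysis for the markers is unadjusted, does not commit to the changes named in the objective, and leaves the recurrence aim without any analysis.

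Its size depends on the shift between arms. With 30 per arm, combined arms and no link within arm, false significance is about 8% at 0.5 SD and 24–25% at 0.9 SD, against about 5% after adjustment. The 34–97% range applies only if baseline and week-8 values are pooled, and it rests on assumed shifts of 1.5–2 SD in PASI and 0.5–1 SD in the marker. It shows what the wording leaves open and is not a forecast for this trial. The absence of a marker-by-recurrence analysis needs no such assumption.

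**What to change.** In section 3.10:

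1. State that, in randomised patients only, week-8-minus-baseline marker change is correlated with week-8-minus-baseline PASI change, one pair per patient, as a partial Spearman correlation adjusted for arm and also shown by arm.
2. For followed patients, add an analysis labelled exploratory of a few prespecified week-8 markers by recurrence status or time to recurrence, adjusted for arm.

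The cost is a few sentences and little programming, with no extra patients. One point needs confirming: the initial-assessment list in section 2 names no cytokine or T-cell sample, and a baseline sample is only implied by the abstract's reference to changes. Table 1 should settle this.

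The downside is that change-based, arm-adjusted correlations will usually be smaller than pooled ones. The recurrence analysis will be imprecise and applies only to patients whose PASI improved by more than 75%, so it can describe but not confirm.

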### Secondary outcomes

3.6

(1)The DQOLS: the DQOLS 4-point scale contains 30 questions, involving psychological activities, such as embarrassment, despair, stress, pain (“very” to “no”) and social activities, such as daily life, social life, sexual life (“very bad” to “normal” or “very few” to “often”) and scoring 1 to 4 points from right to left. The cumulative score ranges from 30 to 100.(2)Score of pruritus degree: patient global assessment (PGA) “How serious is your skin pruritic now?” The patient's answer ranges from “no pruritic” to “intensively pruritic” and can be given with a score of 0 to 6.(3)Safety Assessment: the routine chemical examinations will be performed in 72 patients, at week 1 and 8 and will involve blood, urine analysis and fecal routine analyses, electrocardiogram, kidney and liver function assessments (ALT, AST, BUN, Cr, TBIL, GLU).

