### Adverse events

3.7

(1)Ask and record the adverse events and degree of patients at each consultation after medication, and record, in details, the symptoms, occurrence, duration and disappearance times of adverse events.(2)The correlation between adverse events and drugs is assessed according to whether they are unrelated, possibly unrelated, possibly relevant, or relevant.(3)Incidence of adverse events = number of adverse events / total cases × 100%.(4)After treatment, the patients’ tolerance to drugs will be evaluated according to poor, moderate, light and high praise.

If adverse events occur or there were abnormal blood test results of liver and kidney function, the subjects will be advised to discontinue all drug treatments related to the test and seek medical advice from doctors for a safe continuation of the study.

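### The rule for secondary outcomes (means, SDs, medians) also covers the safety tests, where it does not fit categorical results and does not count patients who became abnormal

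*Protocol article*

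**What the plan says.** Section 3.6 (Secondary outcomes) lists three items: the DQOLS quality-of-life score, the pruritus score and the safety assessment. The third begins "Safety Assessment: the routine chemical examinations will be performed in 72 patients, at week 1 and 8". Besides blood and urine analysis it covers "fecal routine analyses, electrocardiogram, kidney and liver function assessments (ALT, AST, BUN, Cr, TBIL, GLU".

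Section 3.10 (Statistical analysis) has one sentence for the class: "The secondary outcomes will be evaluated by means, standard deviations and medians". It makes no exception for the safety item. The categorical method in that section goes elsewhere: "The Chi-square test will be used to evaluate the basic baseline characteristics and primary outcomes of the 2 groups". The other between-group method also works on means: "The one way ANOVA test will be used to compare the mean of multiple samples".

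Section 3.7 (Adverse events) handles safety separately. It defines "Incidence of adverse events = number of adverse events / total cases × 100" per cent. It also has a management sentence that opens "If adverse events occur or there were abnormal blood test results of liver and kidney function" and goes on to advise such patients to discontinue the trial drugs and seek medical advice.

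**The concern.** The rule in section 3.10 suits two rating scores. Applied to the safety item, it meets two kinds of data that it does not serve well.

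- **Results recorded as categories.** An ECG read as normal or abnormal, or a urine or stool finding recorded as present, absent or graded, needs counts. A mean and SD of such a result carry no usable information.
- **Continuous chemistry.** An arm mean, SD and median describe the distribution as a whole. The safety question is how many patients moved from inside to outside the reference range, and section 3.7 itself treats an individual abnormal liver or kidney result as important.

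The abstract makes the value of the granules conditional on a lower recurrence rate with no added harm, against an active comparator. Laboratory and ECG findings are part of the evidence on harm, and the stated summary leaves out the patient counts that would support that part of the conclusion.

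**Working it through.** The plan gives no figure to reproduce. The check compares the passages and then uses an illustration with assumed values.

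**Passages side by side**

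| Question | 3.6 | 3.7 | 3.10 |
|---|---|---|---|
| Are the safety tests a secondary outcome? | Yes, item 3 | – | – |
| Summary for secondary outcomes | – | – | Mean, SD, median |
| Categorical method | – | – | Chi-square, for baseline characteristics and primary outcomes |
| Count of patients with an abnormal test | None | None; abnormal liver or kidney results are named next to adverse events | None |

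The safety tests therefore fall under a rule for continuous data, and the article gives no count or proportion of abnormal results for any of them.

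**Illustration for a continuous analyte**

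Inputs: n = 36 per arm (section 3.8). All ALT values, and an upper limit of normal of about 40 U/L, are assumptions, because the article gives none.

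Case A: 33 patients at 20 and 3 at 120.
- Mean = (33 × 20 + 3 × 120) / 36 = 1020 / 36 = 28.3
- SD = √{[33 × (20 − 28.33)² + 3 × (120 − 28.33)²] / 35} = √(27,500 / 35) = 28.0
- Median = 20.0
- Patients affected: 3/36 = 8.3%

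Case B: 34 patients at 20 and 2 at 150.
- Mean = (34 × 20 + 2 × 150) / 36 = 980 / 36 = 27.2
- SD = √{[34 × (20 − 27.22)² + 2 × (150 − 27.22)²] / 35} = √(31,922 / 35) = 30.2
- Median = 20.0
- Patients affected: 2/36 = 5.6%

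Case C: 35 patients with mean 25 and SD 8, and 1 at 200.
- Mean = (35 × 25 + 200) / 36 = 1075 / 36 = 29.9
- SD = √{[34 × 8² + 35 × (25 − 29.86)² + (200 − 29.86)²] / 35} = 30.2
- Patients affected: 1/36 = 2.8%

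B and C have the same SD to one decimal, yet two patients are affected in B and one in C. C has the highest mean of the three and the fewest affected patients. In all three cases the mean is below the assumed limit. The SD shows that something extreme is present. None of the three statistics gives the number of patients, or whether they were normal at week 1.

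**Does the section 3.7 incidence fill the gap?** Its wording joins adverse events and abnormal liver or kidney results with an *or*, and nowhere says that the second are counted among the first. The formula divides events by cases, so even if they were counted it would not give the number of patients affected, nor a result for each test.

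**The case against.** The strongest reply has four parts.

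1. *The rule is not exclusive.* Section 3.10 does not say that these are the only summaries, and a condensed article may leave tables of abnormal results to a fuller document. This stands in part: a reader might infer that the plan restricts the safety report to these statistics, and the text does not say so. But the article states a method for the class, gives no other for these tests, and assigns its categorical test to other outcomes. That is an unsuitable stated rule, and goes beyond missing detail.
2. *Safety is reported elsewhere.* Section 3.7 plans an incidence, a causality grading, event details and a tolerance rating, and section 2 has adverse events collected at weeks 2, 4, 6 and 8. This stands. A reader might infer that the safety half of the conclusion would be wrong or absent, and the article does not support that. Nor are individual abnormalities hidden from clinicians, since section 3.7 provides for a response to them. The gap is confined to the planned group summary of the tests.
3. *The SD would give a warning.* This stands. An SD close to or above the mean, with the mean well above the median, is visible to any careful reader, so it goes too far to say that an affected arm would simply look normal. What remains is that the SD does not count patients.
4. *The recording format is unknown.* This also stands. The article does not say how ECG, urine and stool results are recorded, and some urine and blood items are quantitative. It cannot be said that the summaries are impossible to calculate for these tests as a group. The point holds for whatever is recorded as a category.

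**Conclusion.** The point holds in a limited form. Sections 3.6 and 3.10 together put the safety tests under a rule that is not meaningful for results recorded as normal/abnormal or graded, and that does not show how many patients became abnormal on ALT, AST, BUN, Cr, TBIL or GLU. The adverse event incidence in section 3.7 reduces the gap but, as worded, does not close it.

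The size cannot be read from the documents. In the assumed ALT examples, between 2.8% and 8.3% of an arm could have marked rises while the arm mean stays under 30. The planned SD (28.0 to 30.2) would prompt questions without answering how many patients were affected. This rests on assumed values and on at least some ECG, urine or stool findings being recorded as categories. The matter concerns reporting of the safety tests and leaves the primary comparison untouched.

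**What to change.** In section 3.10, take the safety assessment out of the general rule for secondary outcomes and state that:

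- each safety test is reported by arm as n (%) of patients with an abnormal result, with a week 1 to week 8 normal/abnormal shift table based on the laboratory reference range;
- means, SDs and medians are kept for the continuous analytes as supplementary description.

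In section 3.7, state whether laboratory abnormalities count in the adverse event incidence.

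Maximum values as multiples of the upper limit, and exact confidence intervals for differences between arms, are optional in a pilot of this size.

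The cost is a few extra tables from results already scheduled, with no added tests or visits. The proportions will be imprecise: with 36 per arm one patient is 1/36 = 2.8 percentage points, and 0 of 36 still leaves an exact two-sided 95% upper limit of 1 − 0.025^(1/36) = 9.7%. No clinical management rule is changed.
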